## Abstract

**Background:**

Acupuncture is effective in symptom and quality of life improvement of chronic asthma, but the efficacy differences between different acupoints are uncertain. In terms of the theory of Meridian-viscera Association, the study aims to investigate the different effectiveness between acupoints in Lung meridian and the acupoints in Heart meridian, so as to provide the evidence to develop a better prescription of the acupuncture treatment of chronic persistent asthma.

**Methods:**

This study is a multicentral randomized controlled trial. A total of 68 chronic persistent asthma patients will be randomly allocated into two groups: the Lung meridian group and the Heart meridian group. This trial will include a 2-week baseline period, a 4-week treatment period with 12 sessions’ acupuncture, and an 8-week follow-up period. The primary outcome is the Asthma Quality of Life Questionnaire (AQLQ). Secondary outcomes are the Asthma Control Test (ACT), Peak Expiratory Flow (PEF), and Forced Expiratory Volume in 1 s (FEV1). The AQLQ and ACT will be collected at baseline, week 4, week 8, and week 12 after randomization. PEF, FEV1, the Self-rating Anxiety Scale (SAS), and the Self-rating Depression Scale (SDS) will be assessed at baseline and week 4.

**Discussion:**

The results will provide evidence for acupuncture prescription selection and the clinical efficacy improvement. The results of this trial will also be used to determine whether or not a full definitive trial will go ahead, which will further confirm the theory of Meridian-viscera Association.

**Trial registration:**

Chinese Clinical Trial Registry (http://www.chictr.org.cn/showproj.aspx?proj=43803) ChiCTR1900027284. Registered on 7 November 2019

**Supplementary information:**

**Supplementary information** accompanies this paper at 10.1186/s13063-020-04844-8.

## Background

Asthma is characterized by bronchial hyper-responsiveness and chronic airway inflammation and accompanied by episodic wheezing, chest tightness, breathlessness, and cough [1, 2]. Asthma is one of the most common chronic respiratory diseases, and its prevalence varied from 0.2 to 21% in different countries [3]. The global prevalence of doctor-diagnosed asthma in adults is 4.3% and estimated to affect more than 300 million individuals worldwide [2]. Asthma not only significantly reduces patients’ quality of life (QoL) [4], leads to substantial disability [5], but also brings a heavy economic burden to patients, their families, and society, especially in low-income and middle-income countries [1, 6, 7]. Asthma is among the leading causes of mortality and morbidity worldwide [5], ranked among the top 20 conditions causing disability globally and ranked the 23rd as causes of disease burden as measured by disability-adjusted life years in 2015 [8, 9].

According to the 2019 Global Initiative for Asthma (GINA) guidelines on the management of asthma [2], current treatment options include asthma education, self-management strategies, elimination of risk factors, and medication control. Pharmacotherapies such as daily inhaled corticosteroids, long-acting inhaled β2-agonists are recommended to control symptoms and reduce the risk of serious exacerbations [2]. However, long-term pharmacological treatment inevitably has some potential side effects, such as adrenal suppression [10], decreased bone mineral density [11], liver toxicity [12], and increased risk of asthma-related death [13]. Therefore, seeking safe and effective therapies for asthma prevention and control aroused increasing concern [14–16].

Acupuncture, as a main complementary and alternative therapy, has traditionally been used to control asthma in China for thousands of years. Recently, accumulating evidence has supported the benefit of acupuncture for asthma [17, 18]. It is reported that acupuncture can significantly relieve the asthma-related symptoms, improve QoL, influence inflammatory cell counts [17], ameliorate of peak expiratory flow (PEF) variability [14], and increase the forced expiratory volume in 1 s (FEV1) [19]. However, most of these studies have focused on whether acupuncture is useful for asthma by comparing the efficacy differences between acupuncture and medication intervention [14, 18], or verum acupuncture and sham acupuncture [15, 17]. Few trials have involved the comparison of different acupuncture prescriptions to verify the efficacy differences between different acupuncture interventions.

According to the theory of traditional Chinese acupuncture, the Lung meridian connects with the lung directly, while the Heart meridian associates with the lung indirectly. Both the acupoints on Lung meridian and on the Heart meridian are commonly used for preventing and controlling asthma in clinical practice [20]. Hence, this multicenter randomized controlled trial focuses on the efficacy differences of the two acupoint prescriptions for treating asthma by evaluating the effectiveness of the acupoints on the Lung meridian compared to the acupoints on the Heart meridian, respectively, so as to provide high-quality evidence for a better acupuncture prescription selection and improve the curative effect.

## Method and design

### Study design

A two-arm, multi-center, randomized controlled trial will be conducted at the First Affiliated Hospital of Chengdu University of Traditional Chinese Medicine (CDUTCM) and the First Affiliated Hospital of Anhui University of Traditional Chinese Medicine. Sixty-eight eligible asthma patients diagnosed with the guide for asthma management and prevention of updated GINA 2019 [2] will be recruited and randomized into two groups with a 1:1 ratio. Outcome assessment will be performed at the baseline and the end of treatment and during the follow-up period. Patients enrolment will be started in November 2019 and is expected to end in October 2021. The details of the study design are shown in Fig. 1.

**Fig. 1 Fig1:**
[figure not shown]
Study flowchart. Eligible patients will be randomly allocated into 2 groups with 1:1 ratio. Clinical data will be acquired at four timepoints: baseline (week 0), the end of treatment (week 4), and at the follow-up period (week 8, week 12). *AQLQ* Asthma Quality of Life Questionnaire, *ACT* Asthma Control Test, *PEF* Peak Expiratory Flow, *FEV1* Forced Expiratory Volume in 1 s

This trial is reported in accordance with the Standard Protocol Items: Recommendations for Intervention Trials (SPIRIT) guidelines [21] (Table 1, Additional file 1) and follows the principles of the Consolidated Standards of Reporting Trials (CONSORT) and Standards for Reporting Interventions in Clinical Trial of Acupuncture (STRICTA) [22]. The study has been approved by the Ethics Committee of the First Affiliated Hospital of CDUTCM (the approved number: 2019KL-045) and was registered at the Chinese Clinical Trial Registry (registration number: ChiCTR1900027284).

**Table 1 Tab1:**
[figure not shown]
Standard Protocol Items: Recommendations for Interventional Trials (SPIRIT) schedule of the trial

This is a randomized controlled trial which includes a 2-week baseline period, a 4-week treatment period, and an 8-week follow-up period. In the baseline period, recruited patients will be screened, and eligible asthma patients will sign an informed consent and receive a physical examination. After allocation, the patients will receive 12 sessions of acupuncture (acupoint of Lung meridian or Heart meridian) during the treatment period. The outcome assessments, AQLQ, and ACT are performed at baseline, at the end of treatment, during the follow-up, and at the end of the follow-up. The outcome assessments, PEF, FEV1, SAS, and SDS are performed at baseline and at the end of treatment. In addition, the asthma dairy should be recorded at any time during the trial if asthma attacks. The first time of emergency medicine taken should be recorded at any time during the follow-up period. The expectation of acupuncture will be assessed at baseline. The physical examination including blood routine test and blood biochemical test will also be performed at the end of treatment to evaluate risks correlated with acupuncture. Adverse events will be recorded at any time during treatment

*AQLQ* Asthma Quality of Life Questionnaire, *ACT* Asthma Control Test, *PEF* Peak Expiratory Flow, *FEV1* Forced Expiratory Volume in 1 s, *SAS* Self-rating Anxiety Scale, *SDS* Self-rating Depression Scale, *EM* Emergency Medicine

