##### Peak Expiratory Flow (PEF) and Forced Expiratory Volume in 1 s (FEV1)

PEF and FEV1 are determined using spirometry and body plethysmography before and after bronchodilation with a short-acting bronchodilator in accordance with recommendations of the national guidelines [29, 30].

The Self-rating Anxiety Scale (SAS) [31] and the Self-rating Depression Scale (SDS) [32] are used to assess the emotion of asthma patients. In addition, the asthma diary including the times, severity, duration of asthma attacks, medication compliance during the trial, and the first time to use the emergency medicine after treatment will also be recorded.

AQLQ and ACT will be evaluated at baseline (week 0), after the intervention (week 4), and at the follow-up (week 8, week 12). The PEF, FEV1, SAS, and SDS will be assessed at baseline (week 0), after the intervention (week 4). The asthma diary will be assessed during the whole trial (week 0– week 12). The expectation for efficacy in patients will be evaluated at baseline [33]. The first time to use emergency medicine after treatment will be evaluated during the follow-up. All the outcome evaluations will be performed by two independent outcome assessors. The two assessors are trained before participating in this trial and blinded to the randomization.

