### Patient safety

Participants with fainting, infection, or other severe adverse events should be discontinued from treatment and processed immediately. Any adverse events will be recorded by patients, acupuncturists, and outcome assessors. Acupuncture related adverse events include bleeding, dizziness, pain, infection, and so on. Besides, any other severe events also will be recorded in the CRFs in detail and be monitored by the Ethics Committees.

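### The schedule text limits adverse event recording to the 4 treatment weeks, while follow-up runs to week 12 and the Patient safety section gives no recording period

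*Protocol article*

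**What the plan says.** The text under Table 1 describes "a 2-week baseline period, a 4-week treatment period, and an 8-week follow-up period". It then gives the collection window for each item. For safety events the rule is "Adverse events will be recorded at any time during treatment". For rescue treatment it is different: "The first time of emergency medicine taken should be recorded at any time during the follow-up period". The section on PEF and FEV1 under Secondary outcomes adds "The asthma diary will be assessed during the whole trial", and it places the AQLQ and ACT assessments at weeks 0, 4, 8 and 12. After baseline, the Table 1 text schedules the blood tests for safety at the end of treatment only.

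The Patient safety section says who records events: "Any adverse events will be recorded by patients, acupuncturists, and outcome assessors". It goes on to say that "any other severe events also will be recorded in the CRFs in detail and be monitored by the Ethics Committees". Neither sentence gives a start or an end date. Data monitoring and management makes the interventionists responsible for monitoring adverse events, and Acupuncture interventions places all 12 sessions within 4 weeks.

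**The concern.** The article does more than leave the adverse event window to the full protocol. It states one, and that window ends when needling ends, 8 weeks before the last assessment. The Patient safety section can be read as wider, but it does not say so. A centre that works from the schedule would stop asking at week 4. A centre that works from the Patient safety section might continue to week 12.

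Two things are at stake. First, an event with delayed onset could be missed or recorded only by chance. The protocol itself lists infection among acupuncture-related events, and an infection from a session late in week 4 could become apparent after the stated window has closed. Second, event counts from centres that applied different windows would not be comparable, and the safety report could not say what period its rates refer to. If both arms within a centre are handled alike, the likelier harm is under-ascertainment and inconsistency between centres, not a bias in favour of one arm.

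**Working it through.** **1. Periods.** Treatment is 4 weeks and follow-up is 8 weeks (Table 1 text). 4 + 8 = 12, which reproduces the last assessment at week 12.

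**2. Windows side by side.**

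| Item | Stated window | Where stated | Reaches weeks 5 to 12? |
|---|---|---|---|
| AQLQ, ACT | Weeks 0, 4, 8, 12 | Secondary outcomes (PEF and FEV1 section) | Yes |
| Asthma diary (attacks, medication compliance) | Weeks 0 to 12 | Same section; Table 1 text | Yes |
| First use of emergency medicine | Follow-up | Table 1 text; same section | Yes |
| Blood tests after baseline | End of treatment | Table 1 text | No |
| Adverse events | Treatment | Table 1 text | No |
| Adverse events of any kind | None given | Patient safety | Not stated |
| Other severe events | None given | Patient safety | Not stated |

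The Table 1 paragraph gives the diary, emergency medicine and adverse events three different windows. Its authors therefore distinguished the trial as a whole, the follow-up and the treatment period, and assigned adverse events to the last of these. This makes it hard to read the treatment window as loose shorthand for the whole trial.

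**3. Who could pick up later events.** The interventionists who monitor adverse events have no described contact with patients after the twelfth session. The outcome assessors do see patients or collect data at weeks 8 and 12, and the Patient safety section names them as recorders. No text, however, makes an adverse event enquiry part of those assessments. The diary's listed content is asthma attacks, medication compliance and first emergency medicine use, so it would not prompt for anything else.

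**4. Size of the uncovered time.** Covered: 4/12 = 33%. Not covered: 8/12 = 67%.

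In patient-weeks, with the planned 68 patients and no dropout (an assumption):
- Treatment: 68 × 4 = 272.
- Follow-up: 68 × 8 = 544.
- Total: 68 × 12 = 816, and 544/816 = 67%.

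For a range, use the plan's own allowance, which leaves 27 of 34 per arm, or 54 patients:
- If all 14 dropouts leave at the end of week 4, follow-up is 54 × 8 = 432, the total is 272 + 432 = 704, and 432/704 = 61%.
- If all 14 leave at randomisation, follow-up is 432, the total is 54 × 12 = 648, and 432/648 = 67%.

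The share of observed time outside the scheduled window is therefore about 61% to 67%.

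**5. What the figure does not show.** The documents give no rate of delayed adverse events, so the number of events missed cannot be estimated.

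**The case against.** The strongest case on the other side has four parts.

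- **No contradiction.** A reader might infer that the schedule and the Patient safety section contradict each other. They do not. One statement has a window and the other has none. The second may mean events of any type within the treatment window, or it may extend beyond treatment. This part stands: the two statements are unreconciled, not contradictory.

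- **Later events are not stated to be lost.** A reader might infer that everything after week 4, including serious events, goes unrecorded. The documents do not support that. Severe events go in the case report forms and are monitored by the Ethics Committees, with no end date, and Data monitoring and management has the committee supervising the trial and its data every 3 months. Attacks and emergency medicine use are recorded in follow-up, and Quality control keeps patients who stop acupuncture under outcome assessment. This stands too, and it narrows the gap to adverse events that are not asthma-related and may not be severe. Even for severe events, though, capture rests on a sentence without a period.

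- **The window has a rationale.** Most listed events (bleeding, dizziness, pain, fainting) would be expected at or soon after needling, and an end-of-treatment check is built in. That is reasonable for those events. It does not answer delayed infection, which is on the same list.

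- **Condensed source.** The Table 1 grid is not shown, and a full protocol presumably gives reporting procedures. That would excuse silence, but here the article states a window. The point can be checked only against the text under the table, and it falls away if the full protocol already runs recording to week 12. In that case the published text still needs correcting.

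**Conclusion.** The point holds in a limited form. As written, scheduled adverse event recording covers the 4 treatment weeks and leaves out the remaining 8 of 12 weeks after randomisation (67%, or 61% to 67% of patient-weeks depending on dropout). Within that time, adverse events other than asthma attacks and emergency medicine use have no scheduled collection point. Severe events may be captured, but over an unstated period.

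The percentage should not be read as the share of harm that is missed. It is a share of calendar or patient time, and the event rate after needling stops may well be low.

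The conclusion assumes that the text under Table 1 reflects its grid, and that no adverse event enquiry is built into the week 8 and week 12 assessments. The primary outcome, sample size, significance level and main analysis are untouched. It is worth correcting because it affects the completeness and comparability of the safety data and is cheap to put right.

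**What to change.** State one adverse event recording period, from randomisation to week 12, and use it in both the Table 1 text (with its grid) and the Patient safety section, covering severe and non-severe events alike. Have the outcome assessors ask about adverse events at the existing week 8 and week 12 assessments and enter the answers in the case report form. They are blinded and are already named as recorders.

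The cost is one enquiry at each of two assessments that already take place, a matching form field, and an edit in two places. No new visit is needed. The downside is slightly more data to collect and review. Trial status describes recruitment as not yet started, so on the article's own account the change could precede the first patient. If enrolment has since begun, it can be made by amendment, with the date recorded so that the safety report can state which patients had the full window.

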### Randomization and allocation concealment

We will use an online or messaging system performed by a clinical information management system (Beijing Bioknow Information Science & Technology Co. Ltd., China) to complete the randomization. When participant-recruiting staffs in sub-center accept an eligible asthma patient, they will enter the patient’s name, gender, age, and medical history in the central randomization system. Then, a random number and an identification code, which are unique for each participant, will be assigned and delivered to the acupuncturists. The allocation number will be concealed from all the participants.

### Blinding

The allocation will be concealed from all the participants. Patients will be told that they will receive one of the two effective interventions randomized after enrolment. As patients in the two groups will adopt different acupoints, interventions of each patient will be performed in separated cubicles to refrain the communication among patients in the two groups and will be asked to wear an eye-patch when they receive treatment. Outcome assessors, data collectors, and statisticians will also be blind to the procedure and result of randomization, group allocation, and intervention. We do not anticipate any requirement for unblinding as the acupuncturist is not blinded, but if required, the Trial Manager, Data Coordinator will have access to group allocations and any unblinding will be reported.

### Participants and recruitment strategy

Participants will be mainly recruited from inpatients and outpatients in the respiratory department of the First Affiliated Hospital of CDUTCM, the Fifth People’s Hospital of Chengdu and the First Affiliated Hospital of Anhui University of Traditional Chinese Medicine. The recruitment strategies also include delivering leaflets at outpatients, posting advertisements in communities, and distributing news on the website of the Chengdu University of TCM and our WeChat public account. All potential asthma patients diagnosed with the GINA criteria will take a physical examination, which includes an x-ray plate, lung function test, electrocardiograph, routine blood test, liver function test, kidney function test, blood immune test (IgE), and urine and feces routine tests. The respiratory physician will make the final diagnosis of potential patients.

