### Inclusion criteria

Patients fulfilling the following 7 items will be included: (1) aging from 18 to 65 years, (2) diagnosed as chronic persistent asthma by respiratory physicians according to the guide of GINA 2019 and medical history, (3) having mild or moderate asthma according to the GINA 2019, (4) having increased in the FEV1 of > 12% and > 200 mL from the pre-bronchodilator value, (5) the FEV1/forced vital capacity (FVC) < 70%, (6) without participating in any other clinical trials or receiving acupuncture due to asthma within 1 month, and (7) having signed informed consent.

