### Exclusion criteria

Patients who match any of the following 8 items will be excluded: (1) be hospitalized in intensive care unit due to acute exacerbation of asthma in the previous 3 months (representing patients at highest risk of adverse asthma outcomes); (2) be diagnosed as other pulmonary diseases such as bronchiectasis, tuberculosis, abscess, cystic fibrosis, alpha 1 antitrypsin deficiency, or restrictive lung disease; (3) having serious cardiovascular diseases such as uncontrolled heart failure, coronary disease, myocardial infarction, severe hypertension, or uncontrolled arrhythmia; (4) having other uncontrolled diseases including liver or kidney or hematopoietic diseases, endocrine and immune diseases, mental disorders, and malignancy; (5) asthma occurs only when accidentally exposed to allergens or chemical sensitizers; (6) having lower respiratory tract infection (e.g., pneumonia) or taking systemic glucocorticoids more than 10 days for severe acute asthma attacks within 1 month before enrollment; (7) currently be pregnant or breast feeding at the time of enrolment or planned pregnancy within the study period; or (8) having any acupuncture contraindications, such as serious atopic, infectious dermatopathy, thrombocytopenic purpura, or hemophilia.

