### Medications

Patients can use the inhaled doctor-directed Seretide (salmeterol and fluticasone) or Symbicort (formoterol and budesonide) as conventional therapy following the respiratory physicians’ instruction. Participants will be not allowed using other interventions during this trial but will be permitted to use inhaled salbutamol or other medication advised by doctors in an emergency. The name of medications, specifications, dose, duration of use, time of symptom relief, etc. will be recorded in details.

There should be at least 6 h between the use of salbutamol and lung function measurements. A stable dose of inhaled glucocorticoids and antihistamines should be maintained for at least 2 months prior to enrollment and during this study. If patients’ desensitization therapy is in the “maintenance” phase, the medication used should be maintained at a stable dose of at least 1 month prior to the enrollment and during this study. Short courses of antihistamine therapy or inhaled glucocorticoid therapy are allowed to treat hay fever. Short-term (< 10 days) use of systemic corticosteroids, aerosol therapy (including β2-agonists, anticholinergics, and steroids), and antibiotic therapy will be permitted during this study.

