### Data analysis

All data will be analyzed by an independent statistician using SAS 9.4 software (SAS Institute Inc., Cary, NC). All efficacy and safety analyses will be strictly conducted according to the intention-to-treat (ITT) principle. Multiple imputation will be used to deal with missing data. Continuous variables will be described with means and standard deviation (SD) or median, maximum, minimum, P25, and P75, as appropriate. And categorical variables will be described with percentage and frequencies.

The comparison between groups will be analyzed by the analysis of covariance (ANCOVA) if the change of outcomes from baseline to 4 weeks is normally distributed. The outcome variable will be the change of AQLQ from baseline to week 4, and covariates will be age, gender, duration of disease, and the expectation of acupuncture in the ANCOVA analysis. The non-parametric ANCOVA will be conducted if the change is not normally distributed. The comparisons between time points within groups will be analyzed using the paired sample *t* test or Wilcoxon rank-sum test, as appropriate. Separate ANCOVA analyses will be performed for each secondary outcome, the AQLQ and ACT at week 8 and week 12 follow-up. Categorical variables will be analyzed using the chi-squared test or Fisher’s exact test, as appropriate.

The center effects will be included in the analysis model. A subgroup analysis between inpatient and outpatient participants in each group will be performed exploratively. Statistical results will be presented as point estimates of effect sizes accompanied by confidence intervals.

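### The primary ANCOVA omits inpatient/outpatient status, a baseline factor the plan itself treats as relevant; adding it, with baseline AQLQ, may gain precision

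*Protocol article*

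**What the plan says.** Under Participants and recruitment strategy, the article names its main source: patients "recruited from inpatients and outpatients in the respiratory department" of three hospitals. Leaflets, community advertisements and online notices come in addition.

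The eligibility rules then narrow this pool. Inclusion criterion (3) is "having mild or moderate asthma according to the GINA 2019". Exclusion (1) removes patients who "be hospitalized in intensive care unit due to acute exacerbation of asthma in the previous 3 months"; no exclusion covers an ordinary ward admission. Exclusion (6) removes lower respiratory infection and "taking systemic glucocorticoids more than 10 days for severe acute asthma attacks within 1 month before enrollment". The Medications section adds: "A stable dose of inhaled glucocorticoids and antihistamines should be maintained for at least 2 months prior to enrollment and during this study".

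The primary outcome is the AQLQ, which asks about the preceding two weeks. The Data analysis section fixes the primary variable as the change in AQLQ from baseline to week 4 and states that "covariates will be age, gender, duration of disease, and the expectation of acupuncture in the ANCOVA analysis". It adds centre effects to the model. Neither inpatient status nor baseline AQLQ is in the list. The same section says: "A subgroup analysis between inpatient and outpatient participants in each group will be performed exploratively".

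**The concern.** A respiratory inpatient who meets the criteria may have been admitted for asthma, because other lung diseases and recent lower respiratory infection are excluded. A patient on an ordinary ward who had a short course of systemic steroids is not caught by exclusions (1) or (6). For such a patient the two-week AQLQ recall at baseline can include the episode that led to admission. Part of the change to week 4 could then be recovery that would occur under either set of points.

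This recovery would fall on both arms alike in expectation. It would still spread the change scores, and in a trial of 68 the inpatients may not divide evenly. A covariate for setting would absorb both effects. The plan must record setting for its subgroup analysis, but does not use it where it would sharpen the primary comparison. A subgroup analysis does not adjust that comparison, and a centre term removes only differences in inpatient mix between centres, not within them.

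**Working it through.** **The plan's own figure.** From the Sample size section: changes of −2.75 (SD 4.52) and 0.86 (SD 4.95), two-sided α 0.05, power 80%. The difference is 3.61, the pooled SD is √((4.52² + 4.95²)/2) = 4.740, and the standardised effect is 3.61/4.740 = 0.762. Then n per arm = 2 × [4.740 × (1.960 + 0.842)/3.61]² = 27.06. The article states 27, and 27/0.8 = 33.75 gives 34. The figures reproduce to within rounding. SDs of this size are hard to square with an overall score that is the mean of 7-point items, so they cannot anchor a calculation in AQLQ points.

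**Assumed inputs.** The article gives none of these:
- inpatient share p: 10% to 50%
- extra inpatient improvement δ: 0.5 to 1.5 AQLQ points
- SD of change within setting: 0.9 points (variance 0.81)

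**Variance explained by setting** = p(1−p)δ² / [p(1−p)δ² + 0.81].

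| p | δ = 0.5 | δ = 1.0 | δ = 1.5 |
|---|---|---|---|
| 10% | 2.7% | 10.0% | 20.0% |
| 20% | 4.7% | 16.5% | 30.8% |
| 30% | 6.1% | 20.6% | 36.8% |
| 50% | 7.2% | 23.6% | 41.0% |

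For example, at p = 0.3 and δ = 1.0: 0.21/(0.21 + 0.81) = 0.206.

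**Effect on the confidence interval.** Leaving setting out widens it by a factor √[1/(1 − share)]: 1.014 at the low corner, 1.12 at the middle case (30%, 1.0 point) and 1.30 at the high corner.

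**Chance imbalance.** With 34 per arm, the SD of the shift in the unadjusted difference is δ√(2p(1−p)/34): 0.036 at the low corner, 0.111 in the middle case and 0.182 at the high corner, against the minimum important difference of 0.52 that the article quotes. This is not a second harm on top of the first. In the middle case the standard error without setting differences is 0.9√(2/34) = 0.218, and with them √(0.218² + 0.111²) = 0.245. The ratio 0.111²/0.245² is again 0.206, so the shift is the variance share in another form.

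**In SD units, with no AQLQ SD needed.** Let D be the extra inpatient change in within-setting SDs. The variance is multiplied by 1 + p(1−p)D². With the planned effect of 0.762 and 27 analysed per arm (normal approximation), power starts at 79.9%. It becomes 79.0% at p = 0.1, D = 0.5; 77.9% at p = 0.3, D = 0.5; 72.0% at p = 0.3, D = 1.0; and 61.0% at p = 0.5, D = 1.5. These take the planning SD as the SD within setting. If the cited study already mixed inpatients and outpatients, its SD would contain this spread, and the covariate would be a gain over plan and its omission no shortfall.

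All these figures assume that the listed covariates and centre absorb none of the setting effect, and that baseline AQLQ is not in the model.

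**The case against.** The strongest objection is that the premises are inferred. The article does not say why inpatients were admitted, how many will enrol or how much they will improve. Recruitment through leaflets, advertisements and online notices may make inpatients few. The stable-dose rule, the mild or moderate criterion and exclusion (6) would screen out many patients who are still recovering. This stands: it is why the size cannot be pinned down and why the lower part of the range is the more plausible.

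It can also be said that if inpatients improve more because they start lower, baseline AQLQ is the more direct covariate and would capture much of the effect. This stands too, and baseline AQLQ is therefore part of the fix. What remains for setting after baseline adjustment would probably be smaller than the figures above.

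A reader might infer that recruiting inpatients contradicts the stable-dose rule. It does not. One passage says where candidates are found and the other says who may enter; an inpatient whose inhaled dose changed within the two months simply does not meet the rule.

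A reader might also infer that randomisation wrongly lacks stratification by setting. The article names no stratification factor at all, and a condensed account commonly leaves such detail to the full protocol. Its silence supports no finding.

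The covariate list is different: the article states it explicitly, so the omission of setting does not rest on silence.

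**Conclusion.** The point holds as a matter of precision. The plan regards setting as worth a subgroup analysis, yet its stated primary model does not adjust for it or for baseline AQLQ. It is tempting to say that the primary comparison is therefore biased. That goes too far: randomisation keeps the estimate unbiased in expectation, and the confidence interval already allows for chance imbalance. What is lost is efficiency.

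The loss lies between negligible (about 3% of variance) and material (about 41%), and the range rests wholly on the assumed inpatient share, recovery and SD. Given the eligibility filters, a small to moderate effect is the safer expectation. Confidence that the change is sensible is reasonable; confidence in its size is low.

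**What to change.** In the Data analysis section, add inpatient/outpatient status at randomisation to the prespecified covariates of the primary ANCOVA, and name baseline AQLQ as a covariate as well. Settle both before anyone sees outcome data by arm. Keep the inpatient/outpatient subgroup analysis as exploratory.

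The cost is one degree of freedom per term, on data the trial already needs. Taking two centres as in the Study design section and one parameter per covariate, the stated model has 7 parameters (intercept, group, four covariates, centre). With 2 × 27 = 54 analysed, that leaves 47 residual degrees of freedom, and 45 after both additions. A covariate that explained nothing would cost roughly 1/47, or about 2% of variance. Setting would therefore about break even at the low end of the range and gain elsewhere. No change to recruitment, eligibility or treatment rules is needed for this point.
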